**Eye Tracking**

The eye tracking component to this study will attempt to answer several research questions. Specifically, does the magnitude of within-subject changes in VSB to smoking cues/and or emotional cues predict successful cessation and long-term abstinence? Does active tDCS change VSB to smoking cues, negative emotional cues or high-arousal/high-risk cues? Are within-subject changes in VSB to smoking/and or emotional cues correlate with the individual’s cravings? Does the individual’s VSB to high-arousal/high-risk cues correlate with long term treatment outcome? Eye movements will be recorded by Visual Attention Scanning Technology (VAST) (EL-MAR Inc. Toronto, Ontario Canada) (Guestrin and Eizenman, 2006, Pinhas et al., 2014, Chau et al., 2016) on five separate occasions (baseline, 4-weeks after start of treatment, 8-weeks after start of treatment,at the end of treatment -12-weeks and 6 months follow up). During each session, we will measure: 1) attentional bias to smoking cues, 2) attentional bias to negative emotional cues, and 3) attentional bias to high-arousal/high-risk cues.

**Free Viewing paradigm**

The eye tracking tests will use the free viewing paradigm for attentional bias assessment that was developed by Eizenman et al., (2003). In this paradigm individuals freely view (i.e., no implied task) multiple visual stimuli that are presented simultaneously and compete for the individual’s attention. Under free viewing conditions, visual scanning behaviour (VSB) is reflective of internal thought processes and closely follow shifts in attention (Kowler, 1995, Posner & Dehaene, 1994). The free viewing paradigm was used to assess attentional bias in studies of patients with eating disorders, mood disorders and Alzheimer disease (Fok, 2012, Pinhas et al, 2014, Chau et al, 2016, Chung, 2015).

*Approximate time for an eye-tracking session*

Setup and subject calibration: 3 min
Attentional bias to substance-related cues: 5 min
Attentional bias to negative emotional cues: 5 min

Attentional bias to high-arousal/high-risk cues: 5 min

Total test time: 18 min

Each test will be preceded by an assessment of withdrawal, mood, and craving (Questionnaire of Smoking Urges (QSU); Tiffany & Drobes, 1991) and an assessment of mood (Profile of Mood States, POMS). During the baseline assessment participants will also complete a questionnaire on sensation seeking behaviour (Sensation Seeking Scale, Zuckerman et al., 1978).

**Eye-Tracking Method**

The visual attention scanning technology (VAST) includes a binocular eye tracking system (Guestrin and Eizenman, 2006) that records eye-gaze positions, a monitor to display visual stimuli, software to process and estimate visual scanning parameters and a monitoring station to control and supervise the progress of the study (Pinhas et al, 2014, Chau et al, 2016). Processing of eye gaze data includes the segmentation of gaze-position data to fixation sequences, the association of fixations with areas-of-interest on the visual stimuli and the calculations of visual scanning parameters (Pinhas et al, 2014, Chau et al, 2016).

During the test, participants sit at a distance of approximately 65 cm from the monitor and are allowed to move their head freely within a relatively large volume (25x25x25 cm^3^). Subjects complete a short (30 sec) eye tracking calibration step in which participants follow a moving target on the screen. Following calibration, participants view a series of 85 slides that are presented on the monitor of the VAST system. Each slide contains 4 images that are arranged in a 2 by 2 configuration. The visual angle subtended by each of the four images (at the 65 cm viewing distance) is approximately 15.5° × 12.2° and the horizontal and vertical separation between any two images is greater than 2.5°. Similar to previous studies (Pinhas et al, 2014, Chau et al, 2016, Chung et al, 2015), 48 slides will be used as test slides (these slides are used to test attentional biases to smoking cues, negative emotional cues and high-arousal/high-risk cues), 32 filler slides will be used to mask the purpose of the experiment, and 5 practice slides will be used at the beginning of the test to familiarize subjects with the procedure. Each slide is presented for 10.5 seconds and the total testing time/subject is approximately 18 minutes.

*Attentional bias to substance-related cues*

Individuals with substance use disorders typically show an attentional bias to substance-related cues. The attention bias is thought to develop as a consequence of a classical conditioning process. One general model of addiction (Franken et al, 2003) suggests that perception of substance-related stimuli lead to increased dopamine level in corticostriatal circuits that draw the subject’s attention towards the perceived substance. The increase in attention promotes craving that further increase the attentional bias. The combination of increased attentional bias and craving increase the probability of substance use and relapse. An Attentional bias towards substance related cues also lead to increase in substance related cognitions (obsessive thoughts about the substance) and to decrease in the ability to execute coping or control strategies that are based on other cues. These two processes work together to increase and maintain an attentional bias towards substance related cues. Most models of addiction (Field et al, 2014) suggest that a) attentional bias for substance-related cues is a characteristic of substance use disorders, b) the bias is associated with the strength of craving at that moment in time and c) strong attentional bias increase the risk of relapse to substance use in those attempting to remain abstinent or to reduce their substance use.

A common paradigm to study attentional bias in substance use disorders is to present subjects with neutral images (desks, pens, etc.) and substance-related images and measure differences between behaviors (reaction time, eye movements) and/or neural activity (EEG, fMRI) when these two classes of stimuli are viewed. We will use the free viewing paradigm and 16 slides to study attentional bias to smoking related cues. Each slide will include an image of smoking related cues (cigarettes, people smoking), an image of a neutral object and two high valence images. The positions (top-left, top-right, bottom-left and bottom-right) of the three different images will be randomly distributed between the slides.

*Attentional bias to negative emotional cues*

According to the affective processing model of negative reinforcement, escape or avoidance of negative affect caused by withdrawal is the principal motive for relapse and renewed smoking (Baker and Fiore, 2004). According to this model as negative affect grows with the length of abstinence it produces biases in attentional processes so that the individual’s attention tends to focus more and more on perceived emotional threats (Baker and Fiore, 2004, Kwak et al., 2007). By monitoring biases in attentional processing to negative or emotionally threatening visual stimuli one can provide an indirect measure of the magnitude of negative affect (the aversive state) in an individual who attempt to withdrawal from smoking. Since the amygdala is integral to the regulation of negative emotions, threatening and sad facial expressions that are often used to elicit amygdala reaction (Haxby et al, 2002) will be used with the free viewing paradigm to study attentional bias to negative emotional cues. We will use 16 slides, where each slide includes an image of a threatening face, a sad face, a happy face and a neutral face. The positions (top-left, top-right, bottom left and bottom right) of the four different expressions will be randomly distributed between the slides. We will use the outcome measures of this test to investigate and compare the treatment effects of varenicline and active tDCS on attentional bias to negative emotions in different sessions. We will also examine the relationship between changes in emotional bias and craving.

*Attention bias to high arousal/high risk cues*

Sensation seeking behavior is common in people with substance use disorders and is correlated with vulnerability to substance addiction (Wingo et al, 2016). Sensation seeking behavior is believed to have a biological basis that is expressed as a need for physiological arousal, novel experience, and a willingness to take social, physical, and financial risks to obtain such arousal (Zuckerman et al, 1979, Bardo et al, 1996). The severity of mal-adaptive patterns of novelty seeking behavior are correlated with substance abuse (Wingo et al, 2016, Stacy et al, 1993) and with vulnerability to the initiation of substance self-administration and compulsive substance use (Belin et al, 2012). Moreover, some studies suggest that sensation seeking behavior can predict treatment outcome and relapse (Ismael et al, 2014, Kahler et al, 2009). We hypothesize that sensation seeking behaviour, as measured by attentional bias to high -arousal/high-risk cues, will be correlated with the probability of remaining abstinent over the long term. To test this hypothesis we will use the free viewing paradigm and 16 slides. Each slide will include an image with high-arousal/high risk scenario, image of a neutral object and two images with positive high valence scenarios. The positions (top-left, top-right, bottom-left and bottom-right) of the three different images will be randomly distributed between the slides. We will study the correlation between attentional bias to high arousal/high risk cues and the standard assessment of sensation seeking behavior (Zuckerman et al., 1978), and also the extent to which tDCS affect novelty seeking behaviour.

**Monetary Delayed Discounting Task**

Individuals can have different discounted values of delayed rewards. In other words, delayed rewards are often interpreted as less valuable compared to an immediate rewards. This phenomenon is called delayed discounting. As such, steep discounters (low value for a delayed reward) are more impulsive than shallow discounters. Numerous previous studies have shown that individuals that smoke, drink or use other drugs of abuse, tend to discount delayed rewards more steeply than non-users (MacKillop et al, 2011; Yi et al., 2010). Delayed discounting is measured by a 27 Item Questionnaire developed by Kirby et al. (1999), a questionnaire that has been validated and used in other studies (Kirby et al., 2004; Myerson et al., 2014). Participants will be completing this survey at baseline, end of treatment and at 6 months follow up.

**Participant compensation**

Participants will be compensated as follow: $20 for baseline assessment (1), $20 per tDCS visit (15 total sessions), $95 per fMRI scans (3 sessions total) and $50 for 6 month follow up visit (1).

**Outcome Measures**

The primary outcome measure will be continuous abstinence from smoking during weeks 9 – 12 as reported at clinic visits during those 4 weeks and confirmed using expired CO. Subjects will be classified as treatment responders if they respond “no” to the question: Have you smoked any cigarettes (even a puff) in the last seven days?

The key secondary outcome measures are:

1. Self-reported 7 day point prevalence abstinence throughout weeks 2 to 12 confirmed by expired CO at each clinic visit. To calculate survival curves we will also collect self-reported continuous abstinence weeks 9 through 26. For weeks 13 to 25, this will be collected via email or text message. For week 26, subjects will attend a brief clinic visit so abstinence can be confirmed with expired CO and urinary cotinine using a semi-quantitative dipstick. We hypothesize that the active tDCS group will have higher rates of abstinence (less relapse) than the sham tDCS group.

2. fMRI: change in Blood Oxygen Level Dependent (BOLD) activation in brain regions known to be associated with drug craving and emotion processing/regulation. MRS: GSH levels measured in a single voxel placed over prefrontal cortex. Fractional anisotropy (FA) values will be extracted from DTI analysis from regions of interest (ROIs) or to form probabilistic tractography for the whole brain. Network maps will be extracted and analyzed from the resting state functional connectivity measure.

3. Eye Tracking tests: changes in attentional bias to smoking-related cues and negative emotional cues. Attentional bias to high-arousal/high-risk cues.

*Self-Report Measures*

Participants will complete the 10-item Questionnaire of Smoking Urges-Brief (QSU-10; Tiffany and Drobes, 1991) and the Minnesota Nicotine Withdrawal Scale (MNSW; Toll et al, 2007) at each treatment session upon arrival and immediately after tDCS. They will complete a Side Effects Checklist ([name] et al., 1995) at the end of each treatment session.

Trait scales to be completed at baseline will include the FTND (Heatherton et al 1991) and Alcohol Use Disorders Identification Test (Saunders et al., 1993), 90-day Alcohol Timeline Followback (TLFB; Sobell and Sobell, 1992); 30-day Tobacco Timeline Followback (adapted from alcohol TLFB); Sensation Seeking Scale (Zuckerman et al., 1978).

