**METHODS**

**Design**

This will be a double-blind sham-controlled two-arm randomized clinical trial. Fifty participants will be randomized (1:1) to each arm. Arm 1 will be active tDCS plus varenicline (n=25) and Arm 2 will be sham tDCS plus varenicline (n=25). Treatment duration will be 12 weeks. Subjects will be required to attend an in person assessment visit. They will then be randomized to a condition. Neuroimaging scans (fMRI) and eye-tracking tests will be conducted in all participants at baseline. Participants will undergo two scans at baseline on different days within the same week: one in a satiated state and one in a non-satiated state. The same tasks will be performed at each scan. s. Following the baseline fMRI scans and eye-tracking tests, subjects will start taking the varenicline simultaneous with starting the tDCS regimen whereby they will come to the clinic every day (Monday to Friday) for the first 2 weeks to undergo the stimulation (active: 20 minutes at 2mA, sham: 30 seconds at 2mA and then nothing). Their target quit date will be at the end of this 2 week period. They will return to the clinic every two weeks for the next 10 weeks for a booster tDCS session and to complete questionnaires. Eye tracking tests will be conducted at the end of the fourth and eighth weeks. At the end of the 12-week treatment period they will undergo a third fMRI scan and eye-tracking tests. For the next 14 weeks they will be contacted weekly by e-mail or text message to report on their smoking status as measured by the 7 day point prevalence abstinence question. “Have you had a cigarette, even a puff, in the last 7 days?” At the 6-month time point subjects will be asked to return to the clinic for a brief visit to confirm smoking abstinence using expired CO and urinary cotinine and to complete questionnaires.

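### The responder rule's seven-day recall, asked at visits two weeks apart, covers at most half of weeks 9–12 and cannot by itself establish continuous abstinence

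*Protocol*

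**What the plan says.** The protocol's Outcome Measures section states: "The primary outcome measure will be continuous abstinence from smoking during weeks 9 – 12 as reported at clinic visits during those 4 weeks", with confirmation by expired CO. The next sentence gives the operative rule: a participant counts as a responder on answering *no* when asked "Have you smoked any cigarettes (even a puff) in the last seven days". It does not say at how many visits that answer is needed, and no CO cut-off is given.

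On visits after the two weeks of daily stimulation, the Design section says: "They will return to the clinic every two weeks for the next 10 weeks for a booster tDCS session and to complete questionnaires". The Participant compensation section counts 15 tDCS sessions in all. Weekly remote reporting comes only after treatment: "For the next 14 weeks they will be contacted weekly by e-mail or text message to report on their smoking status".

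Three other smoking measures bear on the point:

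- The Pharmacological treatment section has smoking behaviour recorded at booster visits, with no recall period.
- Key secondary outcome 1 plans a self-reported continuous-abstinence item for weeks 9 to 26, to build survival curves. It names a collection route for weeks 13–25 and for week 26, but none for weeks 9–12.
- The tobacco Timeline Followback is listed among the baseline scales only.

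Key secondary outcome 1 also includes: "Self-reported 7 day point prevalence abstinence throughout weeks 2 to 12 confirmed by expired CO at each clinic visit".

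**The concern.** The outcome is named as continuous abstinence over four weeks, but the rule that decides who has achieved it looks back one week at a time from visits two weeks apart. A participant can smoke in the gap, truthfully answer *no* at the next visit, and be a responder.

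This error runs one way: it turns non-abstainers into responders and never the reverse. That matters here because the Sample Size section says the study's main purpose is to establish an effect size from which a later sample size will be worked out. The Hypotheses and the eye-tracking analysis also compare participants who quit in the last four weeks of treatment with those who did not. If those groups are formed with the same rule, the misclassification passes into those comparisons.

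**Working it through.** **1. Visit schedule.** Ten weekday sessions in weeks 1–2, then one every two weeks for ten weeks, puts boosters at weeks 4, 6, 8, 10 and 12 (days 28, 42, 56, 70, 84). Check: 10 + 5 = 15 sessions, which agrees with the Participant compensation section.

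**2. Days covered.** Weeks 9–12 are study days 57–84, or 28 days.

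| Source | Days asked about | Days inside the window |
|---|---|---|
| Week-8 visit, 7-day recall | 50–56 | 0 |
| Week-10 visit, 7-day recall | 64–70 | 7 |
| Week-12 visit, 7-day recall | 78–84 | 7 |
| Weekly messages | after week 12 | 0 |

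If *no* is required at both visits, 14 of 28 days (50%) are covered; days 57–63 (week 9) and 71–77 (week 11) are not. If only the week-12 answer counts, 7 of 28 (25%) are covered. Moving the week-10 visit by three or six days in either direction still leaves 14 days covered.

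**3. How often lapses would be missed (timing is an assumption).** If *k* lapse days fall at random in the 28, the chance that all of them miss the asked days is C(14,k)/C(28,k) with both answers required, and C(21,k)/C(28,k) with week 12 alone.

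| Lapse days | Both visits required | Week 12 only |
|---|---|---|
| 1 | 50% | 75% |
| 2 | 24% | 56% |
| 3 | 11% | 41% |
| 5 | 2% | 21% |

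**4. Effect on the abstinence rate (weekly risk *q* is an assumption).** Among participants otherwise abstinent, with independent weekly lapse risk *q* and both answers required, the rule passes (1−q)² while true continuous abstinence is (1−q)⁴.

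| q | Rule | True | Overstatement |
|---|---|---|---|
| 5% | 0.903 | 0.815 | 9 points |
| 10% | 0.810 | 0.656 | 15 points |
| 20% | 0.640 | 0.410 | 23 points |

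At the other extreme, suppose every lapse carries into the following week. A week-9 lapse is then caught at week 10 and a week-11 lapse at week 12, so with both answers required the overstatement is 0.

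**5. Effect on the arm difference.** The protocol's own figure comes first: 40% v 80%, 25 per arm, two-sided 0.05, 80% power. The pooled formula gives n = [1.96·√(2×0.6×0.4) + 0.8416·√(0.24+0.16)]² / 0.40² = 22.3, so 23 per arm. At 25 per arm power is 84.5% (78.8% by Fisher's exact test). The stated figure reproduces and is not in dispute.

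Let a share *f* of those not continuously abstinent pass the rule, equal in both arms. The observed rate is p + f(1−p). At f = 10%: 0.40 + 0.10×0.60 = 0.46 and 0.80 + 0.10×0.20 = 0.82.

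| f | Observed rates | Difference | Power, 25 per arm |
|---|---|---|---|
| 0% | 40% v 80% | 40 points | 84.5% |
| 5% | 43% v 81% | 38 | 81% |
| 10% | 46% v 82% | 36 | 77% |
| 20% | 52% v 84% | 32 | 69% |
| 30% | 58% v 86% | 28 | 60% |

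The documents give no value for *f*.

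**6. Week 2.** The target quit date is the last day of the two weeks of daily stimulation. A seven-day window reported in week 2 therefore lies before the quit date.

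**The case against.** Several stronger conclusions are tempting, and the documents do not support them.

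- *Weeks 9 and 11 are never asked about, and lapses in them are lost from the survival curves.* A reader might infer this from the responder question alone. But the protocol separately plans self-reported continuous abstinence from week 9 for those curves, and records smoking behaviour at boosters. The missing collection route for weeks 9–12 is a gap; it does not show that lapses are lost.
- *Lapsed participants in general count as abstinent.* If *no* is needed at both visits, only those whose smoking falls wholly in week 9 and/or week 11 pass. Anyone who smoked in week 10 or 12 is caught, provided the answer is accurate.
- *The rates are inflated by 9 to 23 points.* Those figures depend on weekly lapses being independent, and lapses that persist bring the overstatement down to zero.
- *The arm difference must be diluted.* That needs similar misclassification in both arms. If the arms differ in the mix of brief lapse and sustained relapse, the direction is not fixed.

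It can also be said that this is a pilot of 50 that does not expect significance, and that the Data Analysis section takes as its critical metric partial η² for a different variable, consecutive days abstinent. So the bias is not shown to reach that estimate. This limits the claimed consequence but does not rescue the rule. The Outcome Measures section still names weeks 9–12 abstinence as primary, and two seven-day yes/no answers could not supply a count of consecutive days either.

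CO confirmation does not close the gap on the protocol's own terms. It is taken on visit days, and nowhere does the protocol say it covers the unasked weeks.

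**Conclusion.** The point stands in a limited form. The responder rule does not measure the outcome it is meant to define: it covers at most 14 of 28 days, and 7 if the week-12 answer alone decides. This follows from the visit schedule and the recall period and needs no assumption beyond visits being kept near schedule. Participants who smoked only in the uncovered weeks can be classed as continuously abstinent, and no other planned smoking measure is tied to the rule.

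The resulting bias can only raise the observed rate in each arm, but its size cannot be determined from the documents. The span from 0 to 23 points is an illustration over assumed lapse patterns with both answers required. The shrinkage from 40 to 36 points at 10% misclassification further assumes equal misclassification in the two arms.

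The week-2 matter is minor and separate: that value describes smoking before the target quit date and should not be read as a post-quit abstinence result.

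**What to change.** Either of two changes to data collection covers all 28 days:

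1. At the week-10 and week-12 visits, ask about any smoking, even a puff, since the last visit. Each answer then spans 14 days.
2. Start the existing weekly e-mail or text question at week 9 instead of week 13.

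Then define a responder as a participant who reports no smoking for all four weeks, with CO confirmation at both visits. State that this same information supplies weeks 9–12 of the continuous-abstinence item used for the survival curves, which closes the missing collection route.

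For the point-prevalence secondary outcome, mark the week-2 value as pre-quit, or begin the abstinence series at the week-4 visit.

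The cost is one reworded question, or four extra automated messages per participant (4 × 50 = 200 in all). No visits are added. The change has to be in place before participants reach week 9, because no later analysis can recover answers that were not collected.

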For the eye-tracking data, gaze position data are processed by VAST into sequences of fixations and saccades and summary statistics of visual scanning parameters are computed. The VAST parameters include: the number of fixations, the average fixation duration, the average saccadic amplitude and the number of transitions for each image type. These parameters are sensitive measures of attentional bias for different visual cues. The outcome measures of this paradigm will be analyzed using a mixed-model analysis of variance (ANOVA). The within-groups factors are the image types (smoking, neutral, high valence) and session (sessions 1, 2, 3,4 and 5) and the between-groups factor is group (active tDCS and sham tDCS). Pearson’s product–moment correlations will be conducted between parameters of attentional bias and subjective craving scores. Through analysis, we will investigate and compare the treatment effects of varenicline and active tDCS on attentional bias in different sessions. We will also examine the relationship between changes in attentional bias and craving.

By means of a mixed design repeated-measures ANOVA, the VAST parameters will be compared within-subjects at 5 sessions to investigate the effects of varenicline treatment. The parameters will also be compared between the two groups of subjects to examine the treatment effects of active tDCS. We will also compare the VSB parameters of those who quit smoking in the last 4 weeks of treatment and those who were unable to remain abstinent to find out the possible indicators of treatment outcome. Pearson correlation method will be used to explore the relationships between: a) subjective craving and VSB parameters, b) sensation seeking behavior as measured by the sensation seeking scale measures and VSB parameters. Also we will use recurrent neural networks (Chung et al, 2018) to analyze differences between fixation sequences of patients that were treated with tDCS and patients that were not, and between patients that quit smoking and those that were not. Using Cox regression of survival analysis, we will also investigate the correlation between the length of abstinence (time to relapse) and VSB parameters associated with smoking cues, negative emotional cues and high-arousal/high-risk cues.

All data analysis will be conducted using SPSS, SPM or R as appropriate.

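### The weeks 9–26 abstinence curve asks about only half the days in weeks 9–12 but every day from week 13, so brief lapses count differently before and after week 12

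*Protocol*

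**What the plan says.** Key secondary outcome 1 in Outcome Measures defines the variable behind the survival curves: "To calculate survival curves we will also collect self-reported continuous abstinence weeks 9 through 26". Three collection schemes feed that span.

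- **To week 12.** The Design section has participants attend two-weekly after the daily phase: "They will return to the clinic every two weeks for the next 10 weeks for a booster tDCS session and to complete questionnaires". Outcome Measures describes the measure at these visits as "Self-reported 7 day point prevalence abstinence throughout weeks 2 to 12 confirmed by expired CO at each clinic visit".
- **After week 12.** "For weeks 13 to 25, this will be collected via email or text message". The Design section makes the contacts weekly: "For the next 14 weeks they will be contacted weekly by e-mail or text message to report on their smoking status". It gives the question as "Have you had a cigarette, even a puff, in the last 7 days". No biochemical check is stated for these weeks.
- **Week 26.** One clinic visit, at which "abstinence can be confirmed with expired CO and urinary cotinine using a semi-quantitative dipstick".

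Data Analysis applies Kaplan-Meier methods to the abstinence data. It also plans a Cox regression on the eye-tracking measures: "we will also investigate the correlation between the length of abstinence (time to relapse) and VSB parameters", where VSB is visual scanning behaviour.

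**The concern.** A 7-day question asked once a fortnight leaves every second week unasked. The curve is labelled continuous abstinence, yet for its first four weeks the stated question cannot establish that. From week 13 it can, subject to truthful answers. The meaning of an event therefore changes within one curve: a short lapse that ends before the next look-back begins is missed before week 12 and asked about after it.

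Part of Research Question 1 is whether active tDCS makes people more resistant to relapse in the long term. The curve's shape and its median time to relapse bear on that question, and the event times also enter the Cox analysis. Some of what these show would reflect the change in questioning. Days never asked about cannot be recovered later by any analysis rule.

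**Working it through.** The protocol gives no figure for this point, so there is none to reproduce. The check is a count of days covered, followed by illustrations on stated assumptions.

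**1. Visits in weeks 9–12.** Participant compensation lists 15 tDCS sessions. Ten are the daily sessions of the first two weeks, leaving 15 − 10 = 5 boosters. At two-week spacing these fall at about weeks 4, 6, 8, 10 and 12, so two fall in weeks 9–12.

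**2. Days covered.**
- Weeks 9–12: 2 visits × 7 days = 14 of 28 days, or 50%. The uncovered days are about weeks 9 and 11.
- Weeks 13–25: 13 contacts × 7 days = 91 of 91 days, or 100%.

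**3. Brief lapses.** Assume one-day lapses, independent from day to day, at a constant rate p per day. This rate is not in the documents. The chance of at least one lapse on an asked day is 1 − (1 − p)^d, where d is the number of days asked about.

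| Assumed p | Weeks 9–12 (d = 14) | Four weeks of weekly contact (d = 28) |
|---|---|---|
| 0.5% | 1 − 0.995^14 = 6.8% | 1 − 0.995^28 = 13.1% |
| 1% | 1 − 0.99^14 = 13.1% | 1 − 0.99^28 = 24.5% |
| 2% | 1 − 0.98^14 = 24.6% | 1 − 0.98^28 = 43.2% |

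At 1%, 24.5 − 13.1 = 11.4% of participants would lapse in weeks 9–12 only on unasked days and still count as continuously abstinent.

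**4. Sustained relapse.** Assume a constant weekly hazard of 0.02, permanent relapse and truthful answers. The share newly recorded is 1 − exp(−0.04) = 3.9% at a two-weekly look and 1 − exp(−0.02) = 2.0% at a weekly look. Events per look halve at week 13, but the rate per week is unchanged. This is a change of date resolution only.

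**5. Week 26.** A simulation of 400,000 people used the same hazard and let a fixed share of relapsers always deny smoking. It assumed that tests at weeks 10, 12 and 26 catch every denier.

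| Assumed denial | Newly recorded at week 25, failed tests counted | Newly recorded at week 26, failed tests counted | Newly recorded at week 26, self-report only |
|---|---|---|---|
| 0% | 2.0% | 2.0% | 2.0% |
| 5% | 1.9% | 3.4% | 1.8% |
| 10% | 1.7% | 4.8% | 1.7% |
| 20% | 1.5% | 7.4% | 1.4% |

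A jump at week 26 needs two things together: failed tests counted as events, and some denial of smoking.

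**The case against.** **Other smoking data are taken at visits.** The Abstract lists self-reported smoking at each study visit, Pharmacological treatment has smoking behaviour recorded at boosters, and Data Analysis mentions consecutive days abstinent. A full day-by-day record would fill the gap. But the protocol does not say that such a record feeds the curve. It lists the tobacco Timeline Followback among the baseline scales only, and the responder rule for weeks 9–12 rests on a 7-day question. Expired CO is described as confirming that answer, not as covering the week before it.

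**Sustained relapse is handled correctly.** This stands. Kaplan-Meier estimates remain right at each look, so the problem is confined to brief lapses and the coarser dates before week 12.

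**Both arms share the schedule under double-blinding.** This stands too. A reader might infer that the treatment comparison is biased; that would need lapse patterns or misreporting to interact with arm, which nothing in the protocol shows. In the Cox model, a step common to everyone is absorbed by the baseline hazard.

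**Verification also changes.** A reader might infer that false reports in weeks 13–25 must all surface as an artificial drop at week 26. The protocol does not support that. It calls the curve variable self-reported throughout and does not say that a failed test overrides the self-report. On a self-report-only reading the jump disappears. How discordant results are dated may also be settled in a statistical analysis plan that is not at hand.

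**Conclusion.** The point holds for the change at week 13. As the protocol stands, the stated question covers 14 of 28 days in weeks 9–12 and every day afterwards; that follows from the schedule without further assumption. Its effect on the curve depends on how common brief lapses are. At an assumed 1% per day the contrast is 13% against 25% over four weeks, and for assumed rates from 0.5% to 2% the later figure is between 1.75 and 1.93 times the earlier one. The damage is to the curve's shape and to event dates for a key secondary outcome. No bias between arms is shown. The week-26 issue is a request for clarification, because a jump there is conditional on an unstated rule and on denial of smoking.

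**What to change.** Send the weekly 7-day question by text or e-mail during weeks 9–12 as well, and name weekly self-report as the event source for the whole curve. The channel and the wording already exist for later weeks. The cost is a small added burden for participants, with no extra visits.

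Add one clarifying sentence on week 26. The simplest course is to keep abstinence verified by CO and cotinine at week 26 as a separate binary outcome outside the curve. If failed tests are to count as relapse in the curve, treat a participant who reported abstinence throughout but fails at week 26 as interval-censored between week 12, the last verified visit, and week 26.
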